##### Sample size

A sample size will not be calculated. The cooperating nursing homes are a convenience sample and well-chosen due to the good and trustful relationship. The aim for recruitment is to involve as many employees and residents as possible. Challenges for recruitment of employees and their compliance is the already high workload which will be already stressed by new tasks and changes in work organization in terms of becoming an ATNH. Residents are considered as a vulnerable group and should be as little burdened as possible. Another challenge here is the fact that many residents are not able to speak and confirm consent for themselves due to dementia or other diseases. In these cases, an authorized person (e.g., a legal guardian) has to confirm consent, which is not under the supervision of university staff.

#### Summative evaluation

As briefly described above, the evaluation focuses on different outcomes at two different levels: (i) employees and (ii) residents, but on non-intended effects as well. Changes due to the complex intervention are expected in job satisfaction of employees in the ATNH compared to control nursing homes. Additionally, there are several changes expected for employees concerning organizational commitment, mental workload or sickness rates and the use of temporary employment agencies. For residents it is expected that the complex intervention will alter quality of care in the ATNH compared to control nursing homes. Further outcomes include the number of nursing home-sensitive hospital diagnoses and apathy symptoms. A full list of all outcomes and instruments is shown in Table 1. All outcomes are measured at baseline, at multiple follow-ups at six-month intervals and at the end of the study (in this case the end of the first phase in 2027). Outcomes are measured via (standardized) questionnaires and/or external assessment by a nurse, and an analysis of resident files and routine data of nursing homes. Sociodemographic data of employees and residents will be collected and analyzed. A secondary data analysis of obligatory quality indicators and external quality audits will be conducted. These internal and external quality indicators (see supplementary material additional file 1) are mandatory in Germany since 2022 and are reported publicly semi-annually. Internal quality indicators include 15 self-assessed items regarding three themes collected by nursing homes and their employees. External quality audits are structured in six themes with 24 items and are collected from assessors and evaluators on behalf of the LTC insurance fund (e.g., Medizinische Dienste/medicproof GmbH).

**Table 1 Tab1:** Overview of outcome and instruments for employees and residents

Outcome	Instruments (Source)
**Employees**	
Job satisfaction	EXQ [26]
Organizational commitment of employees	
Individual commitment of employees	
Collective commitment of employees	
Mental workload	COPSOQ [27]
Employees’ influence and development opportunities	
Employees’ skills	Self-developed
Readiness of digital technology	Self-developed according to [28]
Use of digital technology	Self-developed based on [29]
Sickness presenteeism and absenteeism	Self-developed
*Indicators of a high workload*:	
i. Sickness rate	Routine data
ii. Staff turnover	
iii. Use of temporary employment agencies	
**Residents**	
Quality of care	Obligatory and publicly reported quality indicators and external quality audits
Number of nursing home-sensitive hospital diagnosis	List of nursing home-sensitive hospital conditions [30]
Apathy symptoms	AES [31]
Quality of life	ASCOT-SCT4 [21], QUALIDEM [32–34]
Behavioral and psychological symptoms of dementia	NPI-NH [35]
*Complications and adverse events in persons in need of care*:	
i. Hospital admissions	Routine data
ii. Emergency medical care	
iii. Falls with injuries	
iv. Pressure ulcer acquired in the facility	
v. Use of psychotropic drugs	
vi. Deprivation of liberty measures	

##### Outcomes employees

*Job satisfaction* is measured using the first item of the Employee Experience Questionnaire (EXQ) [26]. This tool allows to obtain a holistic picture of employee experience at work, which describes major perceptions, attitudes and behaviors of employees in organizations. The score ranges from 1 (completely unsatisfied) to 7 (completely satisfied). Higher scores indicate better job satisfaction.

###### Organizational commitment of employees, individual commitment of employees, collective commitment of employees

The EXQ is also used for the following outcomes: organizational commitment of employees, individual commitment of employees, collective commitment of employees. Again, scores range from 1 (no agreement at all) to 7 (full agreement), and higher scores indicate better commitment.

###### Mental workload, employees’ influence and development opportunities

The German version of the Copenhagen Psychological Questionnaire (COPSOQ) is utilized for the measurement of mental workload, the employees’ influence and development opportunities [27]. Four main topics are addressed, personal and workplace details, details of work and activities, questions about work and health, and at last free-text options. The scale ranges from 5 (always) to 0 (never/nearly never). Higher scores indicate a higher mental workload and higher influence and development opportunities.

###### Employees’ skills, readiness for and use of digital technology and presenteeism and absenteeism

A self-developed survey to measure employees’ skills is used. Included questions address qualification, advanced training or other acquired skills and years of professional experience. Readiness for digital technologies includes a short scale according to Neyer et al. [28]. Use of technology is measured via a self-developed questionnaire based on Braeseke et al. [29]. Sickness presenteeism and absenteeism is measured via three self-developed questions.

###### Indicators of a high workload

Due to the complex organizational change in staff, changes in indicators for a high workload, like sickness rate, staff turnover and the use of temporary employment agencies are expected at end of the study. To some extent, it is possible that during the restructuring process of staff deployment and shortly after implementation, the indicators for a high workload show an increase instead of a decrease. These non-intended effects are based on the fact that learning and getting used to new workflows initially leads to additional work and only later to positive effects (J-curve effect).

##### Outcome residents

###### Quality of life

Quality of life will be assessed either using the Adult Social Care Outcomes Toolkit (ASCOT-SCT4) [21] or QUALIDEM (Quality of life in dementia) for people with mild or severe dementia, if residents’ abilities or cognitive skills are not sufficient to complete the ASCOT-SCT4 (due to dementia or other diseases). If QUALIDEM is used, a familiar care-giver will first evaluate the resident’s grade of dementia via the Global Deterioration Scale (GDS) [36] and afterwards complete the QUALIDEM questionnaire for a resident. An overall score and scores for each subscale will be calculated. Depending on an overall scale or a subscale the score assumes higher or lower quality of life for people in need of long-term care [32].

###### Nursing home-sensitive hospital admissions

Nursing home-sensitive diagnoses are defined as diagnoses, which could have been preventable in at least 70% of all hospitalizations with such a diagnosis, if care in nursing homes had been adequate before. Bohnet-Joschko et al. (2022) published a list of 58 several diagnoses which are assigned to nursing home-sensitive hospital admissions [30]. We will collect some basic information about residents, including hospital admissions, to compare these with the list of Bohnet-Joschko et al. (2022).

###### Apathy symptoms

The German version of the Apathy Evaluation Scale (AES) is used to assess apathy symptoms. Apathy can occur as an independent syndrome or is usually associated with other clinical disorders. The AES is a syndrome-independent scale which claims to assess levels of apathy in several disorders. The score ranges from 0 (not applicable at all) to 4 (very applicable). Higher scores assume few to no symptoms [31, 37].

###### Behavioral and psychological symptoms of dementia

The Neuropsychiatric Inventory Nursing Home Version (NPI-NH) is used to characterize the neuropsychiatric symptoms and psychology of patients with Alzheimer’s disease or other forms of dementia for people living in nursing homes. The NPI-NH includes ten behavioral areas and two types of neurovegetative variations. Scores are made for frequency (range 1 - 4 (rarely to very often)), severity (1 - 3 (mild to severe)), occupational disruptiveness and care-giver stress (0 - 5 (not at all to very severely or extremely)). Calculating is based on the author’s recommendations [35].

###### Quality of care in nursing homes

The quality of care is evaluated via the results of internal quality indicators and external quality audits (see supplementary material additional file 1). The reports of quality indicators and quality audits are mandatory and publicly available.

*Complications and adverse events for people in need of care* include hospital admissions, emergency medical care, falls with injuries, pressure ulcer acquired in the facility, use of psychotropic drugs, and deprivation of liberty measures. Routine data of nursing homes are used to assess changes in complications and adverse events. Routine data are collected by nursing homes in any case.

#### Formative evaluation

The formative evaluation aims to illustrate the development of structures, the acceptance of the new structures, and the achievement of specific aspects of the TCALL initiative, as well as to reflect on the dissemination concept. To this end, research diaries are maintained, focus groups and event reflections are conducted, and digital marketing metrics are analyzed.

##### Research diaries

Specially assigned TCALL staff in nursing homes (TIA) regularly keep research diaries and reflect on their daily routines, on daily work routine of employees and on care situation of residents. With these diaries actual conditions and needs can be determined and care-giving in nursing homes can be monitored continuously. Research diaries include key questions which are answered every two weeks and focus questions on special topics whenever needed and useful (Table 2). Results of the research diaries will be clustered and summarized into fact sheets. These fact sheets will be presented to employees and residents and finally discussed and validated in workshops (six months interval).

**Table 2 Tab2:** Questions for research diaries

**Key questions (two weeks response frequency)**	
1	What were your experiences in the last two weeks in the ATNH?
2	What are your current tasks as a TIA?
3	What challenges do you have to face as a TIA?
4	Have you observed any changes in the ATNH in the last two weeks? (Please explain your answer briefly)
5	What else would you like to tell us?
**Focus questions (three months response frequency)**	
	*Self-reflection of TIAs concerning skills*
1	What further knowledge is required to perform better as a TIA?
	*Integration in ATNH*
2	What is helpful to be accepted as a TIA in your nursing home?
3	To what extent have these conditions been met so far?
	*Development of the ATNH*
4	What developments regarding the ATNH have been observed in the facilities up to date?
5	What ATNH-related topics is the organization currently working on?
6	How are the developments in relation to the ATNH accepted and how do you notice it?

##### Focus groups

Focus groups will be conducted with employees, residents, head of nursing homes, TIAs and research staff at least once a year. Perceptions of one’s own role, the acceleration and process of introduced innovations is reflected here. Results are discussed and validated by participants and will be analyzed for further evaluation on themes like process evaluation, acceptance and success or failure of implemented innovations.

#### Health economic evaluation

The health economic evaluation aims first, to calculate the expenses of the intervention and second, to relate the outcomes of the intervention to its costs (cost effectiveness analyses). In doing so, it is essential to distinguish between the costs of the interventions and the costs of the study, particularly the costs of the evaluation of the initiative. While TIAs are necessary for sustainable ATNH and the costs of ongoing innovations and their evaluation are also part of the intervention, the evaluation of the TCALL initiative as a whole and the dissemination are study costs, which have to be treated differently. For the measurement of effects data from the summative evaluation is used. Costs do not only include direct intervention costs, but also the costs of TIAs and all measures necessary for a sustainable structure of the ATNH. As far as outcomes can be measured in monetary terms (e.g., reduction in sickness rate) cost-benefit analyses are conducted from the perspective of the nursing home. With respect to the reduction of hospital admissions cost-benefit analyses from a societal perspective are added.

#### Statistical analysis

The statistical analysis examines the changes in the outcomes in both groups, i.e., employees and residents, in t0 compared to t1-t6 and checks whether these changes differ between the intervention and control groups (difference-in-difference approach). Via correlation analyses we also analyze correlations between different outcome measures as e.g., job satisfaction and quality of care. Confounders will be controlled via regression analyses.

Information conducted within the formative evaluation especially from focus groups will be analyzed descriptively. Click rates and social media views are counted and analyzed with several digital analysis tools and programs to evaluate the dissemination activities.

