### Evaluation

#### Study design and participants

The basic methodology is a systemic evaluation approach [22], which combines both qualitative and quantitative research elements. The intended restructuring in the nursing homes can affect different, sometimes ethically relevant impact dimensions such as the quality of care for highly vulnerable people but also working conditions and processes. These dimensions will be captured using quantitative (standardized questionnaires) and qualitative methods such as focus groups and research diaries to gain further insights from residents, employees, nursing home management and TIAs concerning the implementation process of the several elements within the TCALL initiative (Fig. 4). For a successful implementation it is essential to fully understand rejecting or driving behaviors of all participating members in order to adapt the implementation process. This can lead to minor or major adaptions in single or multiple parts of the TCALL initiative. Additionally, qualitative methods support the participative, co-creative approach and will ensure that all participants (but especially the employees) feel valued and help changing and shaping the restructuring processes in nursing homes. In contrast to laboratory conditions, it is of great importance to address essential disruptive factors in everyday care immediately in order not to jeopardize the initiative and to keep employees and management motivated. An explanatory sequential mixed-methods design with an embedded quasi-experimental long-term study is used for the evaluation of this complex intervention to ensure that aspects of the quantitative results are interpreted correctly and to have reference points when contradictory results occur [23]. The study design also takes into account that confounding factors can influence the assessment of the outcomes. An important factor here has been the pandemic situation of the last few years, which has had a major impact on the care situation in LTC [24, 25] as well as changes in care policy, such as the implementation of new staffing ratios and their financing (Paragraph 113c of the German Social Code, Part 11). In order to avoid bias in the evaluation of the initiative, which may be associated with future changes, a matched control group is integrated into the evaluation.

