##### Eligibility criteria

Participants in this study can be either employees or residents in selected nursing homes (three ATNH and three matched controls). Inclusion criteria for employees is to have worked in the nursing home for at least four weeks prior to the start of the survey. This is intended to prevent positive and negative effects on the employees’ job satisfaction that may arise when starting a new job. No further exclusion criteria is used. Residents can participate in the study if the residents themselves or an authorized person (such as a legal guardian) confirm written informed consent. For ethical reasons care recipients at the end of their lives are excluded, and those who have been living in the nursing home for less than six weeks. This is due to the fact that a change of setting and living situation might have a positive or negative impact on the quality of life, depending on the previous situation at home.

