##### Recruitment

Three nursing homes, which already report a high-quality standard and have a high and qualified staff ratio in order to avoid overloading of the nursing homes, have been selected to become the first ATNH (convenience sample). They were chosen as good and trustful relations with these nursing homes and their management already existed. The nursing homes are located in Bremen and are non-profit organizations. The nursing homes of the control group will be matched to the intervention group (number of beds, costs for residents and located in Bremen). The recruitment for the control group is ongoing.

Participation in the study is voluntary and based on written informed consent. Residents of the intervention group will be recruited by management, employees and TIAs. Management and employees of the intervention group have been informed in person at information events held by the study team in the participating nursing homes. The aim of these events was to inform management and staff of the nursing homes about the TCALL initiative and to enlist support from them. The control group will be recruited and informed by the scientific staff of the University of Bremen and the management of the control nursing homes.

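### The analysis section describes person-level comparisons and makes no provision for the nursing home, although treatment varies only between three and three homes

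*Protocol article*

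**What the plan says.** The Eligibility criteria section sets the structure: "Participants in this study can be either employees or residents in selected nursing homes (three ATNH and three matched controls". The intervention homes are a convenience sample, and under Recruitment the controls are chosen at home level: "The nursing homes of the control group will be matched to the intervention group (number of beds, costs for residents and located in Bremen".

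The Statistical analysis section of the protocol article then sets out three things:
- The effect analysis takes each later wave against baseline, for staff and for residents, and "checks whether these changes differ between the intervention and control groups (difference-in-difference approach".
- A second analysis relates outcomes to one another, and its example pairs a staff survey item with a result of the home: "Via correlation analyses we also analyze correlations between different outcome measures as e.g., job satisfaction and quality of care".
- On adjustment there is a single short sentence, which does not say at what level it applies: "Confounders will be controlled via regression analyses".

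The section names no home term, random effect, cluster-robust variance or small-sample method. Nor does it say that the individual is the unit of analysis or that observations are taken as independent. The Sample size section gives no calculation and aims for as many employees and residents as possible. Strengths and limitations discusses convenience sampling, nurse workload and self-evaluation, but not the number of homes.

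**The concern.** The intervention restructures whole homes. Everyone in a home shares its management, its transformation and innovation agent, and whatever else happens there between two waves. Difference-in-differences removes stable differences between homes. It does not remove a change peculiar to one home, such as a new manager or a staffing gap, and with three homes per arm a few such changes can look like an effect. A person-level analysis counts each respondent as separate evidence about the intervention and so understates this uncertainty. Recruiting more people per home, which is the stated aim, makes the understatement worse.

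The outcomes fall into three cases:
- **Measured on persons** (job satisfaction, quality of life): the inflation described here applies.
- **Available only per home** (quality of care from published indicators and audits; sickness rate, turnover and agency use from routine data): no inflation of this kind, but only six units.
- **Correlation of job satisfaction with quality of care**: one measure belongs to persons and the other to the home, so they can be linked only as home-wave values.

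The evaluation is meant to give external evidence of added value and to help legitimise continuation, and its effect estimates feed the health economic evaluation. Overstated certainty would carry into both.

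**Working it through.** **Inputs from the article:** 3 intervention and 3 control homes (Eligibility criteria); change from t0 compared between groups (Statistical analysis). The article states no sample size, power or alpha, so there is no figure of its own to reproduce.

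**Assumptions, not in the article:** two-sided alpha 0.05; n respondents per home and wave; a share rho of total variance at home-by-wave level; waves treated as independent samples of people.

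**Step 1. Variance of the difference-in-differences, in units of the outcome variance.**
- Person-level (naive): 4/(3n).
- With home-by-wave variation: 4/(3n) × D, where D = 1 + (n − 1) × rho.

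**Step 2. True type I error of the naive test** = 2 × [1 − Φ(1.96/√D)].

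| n | rho | D | √D | 1.96/√D | True type I error |
|---|---|---|---|---|---|
| 40 | 0 | 1.00 | 1.00 | 1.96 | 0.050 |
| 40 | 0.01 | 1.39 | 1.18 | 1.66 | 0.096 |
| 40 | 0.02 | 1.78 | 1.33 | 1.47 | 0.142 |
| 40 | 0.05 | 2.95 | 1.72 | 1.14 | 0.254 |
| 60 | 0.01 | 1.59 | 1.26 | 1.55 | 0.120 |
| 60 | 0.02 | 2.18 | 1.48 | 1.33 | 0.184 |
| 60 | 0.05 | 3.95 | 1.99 | 0.99 | 0.324 |

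With n = 20 the error is 0.072, 0.095 and 0.160 at rho = 0.01, 0.02 and 0.05. Simulation of the n = 40 case gives 0.099, 0.143 and 0.253 at those three values.

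**Step 3. Alternatives, by simulation under no effect.**
- A t test on home-level changes, 3 versus 3 on 4 df (critical value 2.78 instead of 1.96), rejects about 5% of the time at every rho tried.
- An ordinary cluster-robust standard error on six homes with a normal reference rejects about 15–16% of the time, even at rho = 0. Naming such an error would therefore not be enough.

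**Step 4. What the valid analysis can detect.** For n = 40 and rho = 0.02 the variance is 4/120 × 1.78 = 0.0593, so the standard error is 0.244 SD. Power of 80% on 4 df needs a noncentrality of 3.76, and 3.76 × 0.244 = 0.92 SD.

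**Step 5. The correlation.** Quality indicators are published semi-annually and the waves run from t0 to t6, so up to 6 × 7 = 42 home-wave pairs could exist. They are repeated values from six homes and are not independent. Neither the number of respondents nor 42 is a valid count of independent observations for a p-value.

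**The case against.** The strongest reply is that the article never says people are the unit of analysis. Employees and residents are simply its two outcome levels, and both difference-in-differences and regression are compatible with home fixed effects, mixed models or home-wave means. A condensed article may leave such detail to a plan not shown here. That much stands: a reader might infer that the study has committed itself to a person-level analysis, and the text does not support this. What remains is that the comparison is described wholly in terms of people, with no place for the six homes that carry it, and that following the text gives invalid error rates. A routine later repair by ordinary cluster-robust errors would also fail.

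Four further points stand and limit the claim:
- The inflation is conditional. It is nil without home-by-wave variation, and neither n nor rho is given.
- It does not reach outcomes recorded only per home.
- A reader might infer that the correlation rests on six data points. Semi-annual reporting over several waves contradicts this; the trouble is mixed levels and dependence.
- A reader might argue from the limited number of ways to allocate six homes. The homes were not randomised, so a permutation p-value has no design basis here.

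The article does concede that self-evaluation lacks external proof of effectiveness. It does not connect that to the number of homes.

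**Conclusion.** The point holds for person-level outcomes, conditionally on an analysis that follows the text. With an assumed 40 respondents per home and wave, the true type I error of a nominal 5% test is about 10%, 14% or 25% at 1%, 2% or 5% home-by-wave variance, and 5% at zero. The direction is certain once homes have their own changes over time; the size depends on figures that the article does not give. For outcomes held only per home, the issue is six units, not inflated numbers. For the job satisfaction and quality of care correlation, p-values that treat people or home-waves as independent would not be valid. Six homes can support estimates with intervals, but hardly confirmatory proof.

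**What to change.** In Statistical analysis:
- State that the home is the unit of inference. For person-level outcomes, compute home-by-wave means adjusted for individual covariates, take each home's change from t0, and compare 3 versus 3 with a t interval on 4 df.
- Alternatively, use a mixed model with home and home-by-wave random effects and small-sample degrees of freedom. Do not rely on ordinary cluster-robust errors with a normal reference.
- Compute the job satisfaction and quality of care correlation on home-wave means and label it descriptive.

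In Strengths and limitations, add that the comparison rests on six homes and gives estimates with intervals, not confirmatory proof.

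The change needs no new data. The price is wider intervals: about 0.9 SD is detectable with 80% power at 40 respondents per home and 2% home-by-wave variance (both assumed, with waves as independent samples). The person-level formula would suggest 2.80 × √(4/120) = 0.51 SD, a precision the design does not have if that variance is present.
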